### 2.8. Outcome Measures

Primary outcome measures are the number of residents who fall (falls) and the number of falls for each participant (fall rate) in 12 months prior to enrollment in the project. All falls are recorded by the residential aged care home and these data will be accessed by the research team. Other outcome measures are the Quality of Life Aged Care Consumers tool (QOL-ACC) [19], The Frail in Nursing Homes (Frail-NH) Scale [20], and the Short-Form Physical Performance Battery (SPPB) [21]. Each allied health discipline has discipline specific outcome measures that are secondary outcome measures along with a measure of pain. See Table 3.

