## 1. Background

In Australia in 2023, 185,127 people were living in residential aged care [1] and complications due to frailty and injury after falls are a significant problem for these residents. Following entry into residential care, 3.7% of people are hospitalised due to falls within 90 days, and 9.8% within a year [2]. Every six months, it is estimated that 50% of people with dementia in residential aged care experience a fall [3], leading to significant financial and social costs [4]. Additionally, around 95% of residents are estimated as being frail or pre-frail [5], which is also associated with negative health outcomes resulting in hospitalisation [6]. People living in residential aged care also often find a discontinuity between what they found meaningful and engaging prior to entering aged care and what they experience in care, which adversely affects their quality of life [7]. There is a need to focus on enabling people in residential aged care to keep engaging in activities they find meaningful [8] and maximising engagement in everyday life.

The Royal Commission into Aged Care Quality and Safety heard that only 24% of people living in residential aged care felt their needs were always met across several care experiences [9]. This contributed to four recommendations calling for increased allied health interventions to meet the unmet needs in residential aged care. Recommendation 37 specifically lists allied health as a service that should be provided in residential care. Recommendation 38 lists thirteen allied health professionals providers should employ or retain. Recommendation 61 recommends changes to the Medicare Benefits Schedule to include allied health service provision in residential care. Recommendation 69 states that allied health care should generally be provided by aged care providers.

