## 2. Methods

### 2.1. Study Design

This is a pragmatic, non-randomised, pre–post design study where six groups of up to 10 participants will start the intervention at different times. Each group will commence a baseline period lasting six weeks. Primary outcome measures will be administered in week 0 (−t_1_) of the baseline period and in week 6 (−t_2_) of the baseline period. The allied health professionals will conduct assessments using the secondary outcome measures during the baseline period, making recommendations for consideration at the case conference held with the resident’s usual General Practitioner. The prescribed allied health intervention/s will last a maximum of 36 weeks with primary outcome measures taken during the intervention period at 12 (t_1_), 24 (t_2_), and 36 (t_3_) weeks, then at 12 (t_4_) and 24 (t_5_) weeks post-intervention. The case conferences will take place in week 1 or week 2 of the intervention period. The timing of the secondary outcome measures will vary depending on the mix of interventions chosen by the allied health professional and the participant needs. See the Supplementary file for further details.

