## 3. Data Analysis

### 3.1. Quantitative Analysis

All statistical analysis will be conducted using R version 4.2.1 (23 June 2022) in Rstudio (version 2023.6.2.561). Baseline demographic and descriptive statistics will be summarised for each group prior to the intervention starting (control phase). Primary outcome measures will be collected twice in the control period at week 0 and week 6. Primary outcome measures will be collected every 12 weeks during the intervention (weeks 12, 24, and 36) and at 12 weeks and 24 weeks post-intervention for each group. Categorical data will be summarised using frequency statistics and will be visualised. Continuous and other numerical data will be visually explored and summarised using sample descriptive statistics, selected as appropriate based on apparent distributions. A mixed-effects model will be computed, with treatment stage (i.e., pre- vs. post-intervention) as a fixed effect and subject as a random effect. Sensitivity analyses will be conducted, which will impute missing data using the “mice” package (version 3.15.0) [34].

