Optometry	Participants will receive an onsite, mobile assessment by an optometrist evaluating visual function (including refraction, confrontation fields, visual acuity, ocular structure (macula and optic nerve lenticular assessment, and intra-ocular pressure) to address visual impairments that may contribute to fall risk. Actions arising from the assessment of visual function may include new spectacle prescriptions or referral of participants for management of ocular disease.
Pharmacy	Participants will receive an onsite medication review by a pharmacist who will provide recommendations regarding the resident’s medication to the participant’s GP, nursing staff, and family members. After the initial medication review, participants will receive a 2-week follow-up visit to understand how medication decisions are implemented in the medication treatment and charts. Each participant will have an initial case conference and then a follow-up visit from the pharmacist every 3 months (online or in person).

**Table 2 healthcare-13-00341-t002:** Associated power based upon *n* = 50 and mean change in the SPPB.

Increase Mean Response After Intervention	Power
2.5	0.99
2	0.94
1.75	0.84
1	0.63

**Table 3 healthcare-13-00341-t003:** Outcome measure summary.

Primary Outcome Measures	
Falls: Number of falls in past 12 months Number of falls during intervention period Number of falls after intervention	
Quality of Life Aged Care Consumers (QOL-ACC) [19]	
Frailty: The Frail in Nursing Homes (Frail-NH) Scale [20] and the and Patient Health Questionnaire (PHQ9) [22]	
Short Physical Performance Battery (SPPB) [21]	
**Secondary outcome measures**	**Allied health discipline**
Short Falls Efficacy Scale—International (Short FES-I) [23]	Physiotherapy
Subjective Global Assessment (SGA) [24] Mid-arm muscle circumference [25,26] Quantitative analysis of dietary intake will be calculated before and after fortification	Nutrition and Dietetics
Canadian Occupational Performance Measure (COPM) [27]	Occupational Therapy
Number of medications (that contributed to increased risk of falls) ceased/changed at case conferences Number of case conferences and pharmacist follow-ups Rate of GP agreement on pharmacist recommendations	Pharmacy
Number of new or updated spectacles recommended Number of referrals arising from vision assessment The National Eye Institute Visual Functioning Questionnaire—25 (VFQ-25 + 10) [28]	Optometry

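### The primary falls outcome is defined only over the year before enrolment and tabulated as counts over unequal periods with no time at risk; if compared unadjusted, those counts change without any treatment effect

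*Protocol article*

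**What the plan says.** All references are to the protocol article.

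- Section 2.8 names two primary falls outcomes: how many residents fall, and "the number of falls for each participant (fall rate) in 12 months prior to enrollment in the project". No other window is given there. On the source of the data it says: "All falls are recorded by the residential aged care home".
- Table 3, under primary outcomes, lists falls as "Number of falls in past 12 months Number of falls during intervention period Number of falls after intervention". All three are numbers, and none has a denominator.
- Section 2.1 sets the calendar. "Each group will commence a baseline period lasting six weeks". "The prescribed allied health intervention/s will last a maximum of 36 weeks". Primary measures are taken during the intervention, "then at 12 (t_4_) and 24 (t_5_) weeks post-intervention".
- Section 3.1 gives the analysis: "A mixed-effects model will be computed, with treatment stage (i.e., pre- vs. post-intervention) as a fixed effect and subject as a random effect". It states no exposure term.
- Section 2.6 expects up to 60 existing residents and 15 new ones, with 20% lost. Section 2.7 says that data collection stops at withdrawal.
- The Abstract says that the primary outcomes are meant to capture change in falls.

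**The concern.** There are two linked problems.

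First, section 2.8 fixes the falls outcome in a period that the intervention cannot affect. This conflicts with the Abstract's aim of measuring change and with Table 3, which adds two later periods. It also gives the label *fall rate* to what it defines as a plain number.

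Second, Table 3's three counts cover periods of different length. A count grows with the time over which it is collected, and so does the chance of having fallen at least once. Without time at risk, a change between periods mixes any treatment effect with the length of the window.

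Falls are among the primary outcomes and stand in the first research question. The design is pre–post with no concurrent control for falls, so nothing else in it would cancel such an artefact.

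**Working it through.** The article states no fall rate, falls effect or falls power, so there is no falls figure to reproduce. The power figures in section 2.6 and Table 2 concern the SPPB.

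**Inputs.** Look-back: 12 months, taken as 52 weeks (section 2.8). Intervention: 36 weeks, stated as a maximum (section 2.1). After intervention: 24 weeks, inferred from the last visit in section 2.1, because Table 3 gives no length. Six-month risk of falling: 50%, from the Background, where "it is estimated that 50% of people with dementia in residential aged care experience a fall". That figure is for people with dementia, whereas any permanent resident is eligible, so it serves only as an illustration.

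**Mean falls, no effect.** With constant rate λ, the expected count in w weeks is λw. The ratio to the look-back is therefore w/52.
- 36 weeks: 36/52 = 0.692, a drop of 30.8%.
- 24 weeks: 24/52 = 0.462, a drop of 53.8%.
- Both later periods pooled: (36 + 24)/52 = 1.154, a rise of 15.4%.

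**Proportion of fallers, no effect.** For Poisson falls, P(at least one) = 1 − exp(−λw), with λ = ln 2/26 per week.
- 52 weeks 0.750; 36 weeks 0.617; 24 weeks 0.473.
- Relative drops: 1 − 0.617/0.750 = 17.7% and 1 − 0.473/0.750 = 37.0%.
- With negative binomial falls and the same six-month risk, the drops are 12.9% and 28.0% (shape 1), or 10.1% and 22.0% (shape 0.5).
- Over an assumed six-month risk of 30% to 70% and all three distributions, the drops run from 5% to 24% (36 weeks) and from 12% to 45% (24 weeks).

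**Incomplete look-back.** Suppose the 15 new residents have m weeks of usable records and the 60 existing residents have 52. Mean look-back is (60 × 52 + 15m)/75 weeks.
- m = 0: 41.6 weeks. Drops 1 − 36/41.6 = 13.5% and 1 − 24/41.6 = 42.3%.
- m = 26: 46.8 weeks. Drops 1 − 36/46.8 = 23.1% and 1 − 24/46.8 = 48.7%.

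**Dropout.** Suppose 20% leave midway through the intervention and everyone has a full look-back.
- Intervention: 0.8 × 36 + 0.2 × 18 = 32.4 weeks. Drop 1 − 32.4/52 = 37.7%.
- After intervention: 0.8 × 24 = 19.2 weeks. Drop 1 − 19.2/52 = 63.1%.

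**With person-time.** The expected rate is λw/w = λ in every period, so the expected change under no effect is 0%, whatever the window, look-back or dropout.

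**The case against.** A reader might infer that the trial will certainly show a spurious fall reduction of 31% to 54%. The documents do not support that, for these reasons.

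- Nowhere does the article say that unadjusted counts will be compared. Section 2.8 uses the word rate, section 3.1 describes the model only in general terms, and an exposure offset may sit in an analysis plan that is not shown. The absence of an offset from the article is not in itself a fault.
- The windows are partly inferred. The intervention length is a maximum and the 24 weeks comes from a visit date. Section 3.1 contrasts only two stages. If post includes both later periods, the artefact changes sign.
- The percentages apply to mean counts. They do not carry over to the proportion of fallers.
- Nothing states that the home lacks records from before admission. Nor is it certain that falls in the six-week baseline are left out: Table 3 gives no anchor for its 12 months, and primary measures are also taken at weeks 0 and 6.
- Any false-positive rate would need an assumed fall rate, dispersion and test that the article does not fix, so none is claimed here.
- Falls are one of several primary outcomes, and the study is sized on the SPPB.

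All of this stands, and it limits the size and certainty of the bias. It does not answer the point about the definition. An outcome and its time window belong in the protocol; here they are stated, and the stated window lies wholly before the intervention. The word rate is no safeguard when the text defines it as a number. That size and sign both turn on unstated choices is itself a reason to settle the definition.

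**Conclusion.** The point holds as a badly stated outcome definition with a conditional bias. What is established from the text is that section 2.8 defines the falls outcomes only before enrolment, that Table 3 lists counts over unequal periods, and that no time at risk is given.

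If those counts are compared without person-time, mean falls drop by about 31% and 54% with no effect. This assumes a constant rate, a full 52-week look-back, the full 36 weeks of intervention and a 24-week period after it. Fallers drop by about 18% and 37% under the Poisson illustration, and less if falls are over-dispersed. With incomplete look-back for new residents, the drop in counts is 13% to 23% and 42% to 49%. With 20% leaving midway, it is about 38% and 63%. Pooling both later periods gives a rise of about 15%.

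The definition should be corrected before the falls data are analysed.

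**What to change.** In section 2.8 and Table 3:

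1. Define the falls outcome in each period (pre-enrolment and baseline, intervention, follow-up) as falls per resident-time at risk, and state the length of the follow-up period.
2. Analyse it with a count mixed model with log time at risk as offset. Negative binomial is one suitable choice; the offset is what matters, and the model family is a preference.
3. Start pre-period time for new residents when records become available, and end time at risk at withdrawal or death.
4. State in which period falls during the six-week baseline are counted.
5. Compare the proportion of fallers over windows of equal length.
6. Keep the 12-month fall history as the baseline value, not as the outcome.

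The cost is wording and a little analysis work, with no new data collection, provided that the home's fall records are dated. The article does not say so, and this should be confirmed.

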### 2.3. Participants

Any new or existing (permanent) resident of the residential aged care home is eligible. Staff at the home will approach any new or existing resident and/or family with a study flyer. The research team will present the study to the residents at the regular residents’ meeting. Participants will register their interest through a register kept by the nursing staff at the home and/or they will be able to contact the research team through contact details listed on the flyer and promotional material posted at the home. All participants and/or their carers, power of attorney, or guardian will be required to give written consent after reading the relevant participant information at which time the Clinical Liaison Manager (who is a Registered Nurse) will consent them into the study and assign them a study number. Residents with a diagnosis of dementia or identified by care staff as experiencing cognitive impairment are eligible. All participants will be screened for cognitive function using the Psychogeriatric Assessment Scale (PAS) [13]. There is no cutoff score for inclusion; however, in some cases, people with severe cognitive impairment will not be able to engage in the allied health program. For example, people who have severe expressive and receptive communication impairment and who are immobile due to dementia. For those residents with severe dementia or on an end-of-life pathway, we will liaise with the relevant medical team and/or staff Registered Nurse to determine if these residents should ethically be considered for the program. Residents who elect not to participate in the intervention will receive their usual medical, health, and lifestyle services as usual.

Participants will be able to discontinue the intervention at any time at their, or their Enduring Power of Attorney’s, request. Participants will be withdrawn from the study if any deterioration in their medical condition makes participation unsafe in the opinion of their General Practitioner.

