### 2.6. SampleSsize

The sample size was calculated using R based on 1000 simulated versions of the study, where the power estimate is the proportion of simulated studies that gave *p* < α for the difference between the pre- and post-intervention stages. Using the Short Physical Performance Battery (SPPB) as the primary outcome measure with 50 subjects, the increased mean responses anticipated with alpha 0.01 are shown in Table 2. This is assuming the following parameters: average response at baseline 5; between-subject SD 2.5; variability in effect between subjects SD 2 (so the effect is 2.5 with SD of 2); within-subject SD of 1; and between-group SD of 2 [18].

We expect up to 60 existing residents will consent to the intervention. The site estimates that 20 new residents will enter the home during the study period, and we estimate 15 of these new residents will consent to the study. With a 20% dropout and loss to follow-up, the highest number of participants to complete the intervention is 60 participants.

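### The pre-intervention falls count spans 12 months of the home's records, but new and recently admitted residents were not in the home for all of that window

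*Protocol article*

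**What the plan says.** Section 2.8 makes falls a primary outcome, both as the number of residents who fall and as "the number of falls for each participant (fall rate) in 12 months prior to enrollment in the project". The source is stated in the next sentence: "All falls are recorded by the residential aged care home and these data will be accessed by the research team". No other source is named. Table 3 lists three falls counts: "Number of falls in past 12 months Number of falls during intervention period Number of falls after intervention".

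On who enters, section 2.3 states: "Any new or existing (permanent) resident of the residential aged care home is eligible". No minimum length of stay is given. Section 2.6 puts consent among people already living in the home at no more than 60. Of about 20 later arrivals, it says: "we estimate 15 of these new residents will consent to the study".

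Section 3.1 plans a mixed-effects model comparing the pre stage with the post stage, with subject as a random effect. It also plans multiple imputation of missing data as a sensitivity analysis. It does not say which pre-intervention period supplies the falls data.

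**The concern.** The window, the source and the eligible population are each fixed in the text, and they do not fit together for every participant. A resident who enters the home during the study has home records only from admission. Falls earlier in the look-back year happened elsewhere and are not in the named source. Existing residents admitted less than 12 months before enrolment have the same gap in part. The problem is not incomplete reporting within the home: the person was not living there.

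At stake is the before-and-after comparison on a primary outcome in a study with no concurrent randomised control. If a short or empty record is read as a full year, the pre count for those residents is too low while their later falls are fully recorded. Filling the gap from family recall would instead give that subset different sources before and after.

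**Working it through.** **Inputs from the article.** Existing residents expected to consent: up to 60 (section 2.6). New residents expected to consent: 15 (section 2.6). Dropout: 20% (section 2.6). Look-back: 12 months, taken as 52 weeks (section 2.8). Intervention: at most 36 weeks (section 2.1).

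**The plan's own figure.** (60 + 15) × (1 − 0.20) = 60 completers, which matches "With a 20% dropout and loss to follow-up, the highest number of participants to complete the intervention is 60 participants". So 75 is the implied number of consenters, and the new-resident share is 15/75 = 20%.

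**Assumed inputs, not in the article.**
- r: new residents' prior-year fall rate relative to existing residents, 0.5 to 2.
- f: fraction of the look-back year that a new resident spent in the home, 0 or 0.25 (13 of 52 weeks).
- All existing residents have a full look-back year.

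**Recorded pre rate as a share of the truth, if the recorded count is treated as a 12-month count:**

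(60 + 15 × r × f) / (60 + 15 × r)

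| r | f | Calculation | Recorded / true | Apparent rate ratio under no effect, equal-time scale |
|---|---|---|---|---|
| 1 | 0 | 60/75 | 0.80 | 1/0.80 = 1.25 |
| 1 | 0.25 | 63.75/75 | 0.85 | 1/0.85 = 1.18 |
| 0.5 | 0 | 60/67.5 | 0.89 | 67.5/60 = 1.125 |
| 2 | 0 | 60/90 | 0.67 | 90/60 = 1.50 |

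In the first row, a true 20% reduction would appear as 0.80 × 1.25 = 1.00, no change.

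**If the windows are not put on equal time.** Raw counts over 36 weeks of intervention against the 52-week look-back, with no effect, r = 1 and f = 0, give 36/(52 × 0.80) = 36/41.6 = 0.87. That is an apparent 13% reduction. The understatement is still present, since a complete look-back would give 36/52 = 0.69, but the net direction is reversed by the unequal windows.

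**With days resident as exposure.** At r = 1 the recorded rate equals the true rate, 60/60 = 1.00 of the truth. If r differs from 1, a simple pooled pre rate still reflects mainly existing residents. With f = 0 it is 1/(67.5/75) = 1.11 of the truth at r = 0.5, and 1/(90/75) = 0.83 at r = 2. This is why a restricted sensitivity analysis is worth having.

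**The case against.** The strongest reply is that nothing in the article says that absent records count as zero falls. Section 2.8 calls the outcome a fall rate, section 3.1 foresees missing data, and exposure denominators are often left to a fuller protocol or analysis plan. This stands as far as it goes: the understatement is conditional on how the count is used. It does not remove the conflict, because no analysis plan can create home records from before admission. If those values are set to missing, about one expected participant in five has no full 12-month comparator.

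A reader might infer that the falls comparison is simply biased against the intervention by 25%. The article does not support that. The figure needs the pre and post periods already to be on equal time while resident time is ignored, and the raw counts listed in Table 3 would give an apparent reduction under no effect. A reader might also infer that new residents spent most or all of the look-back year elsewhere. No admission-to-enrolment interval is given and group starts are staggered, so someone who enrols a year or more after admission would have a full record.

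It can also be said that primary outcomes are measured twice in the six-week baseline, when every participant is in the home. That is correct (sections 2.1 and 3.1), but Table 3 lists no falls count for that period. For 15 new residents it amounts to 15 × 6 = 90 person-weeks, about 1.7 person-years.

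**Conclusion.** The concern holds as a conflict between stated rules on a primary outcome: the named source cannot give a full 12-month count for residents who were in the home for less than 12 months before enrolment. That covers the 15 expected new residents (20% of 75), subject to when they enrol, and an unstated number of existing residents.

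If the recorded count is used as a 12-month count on an equal-time scale, the pooled pre rate falls to about 0.80 of the truth with equal fall rates and no in-home look-back. The range is 0.67 to 0.89 for relative rates of 2 down to 0.5, and the figure is 0.85 with 13 weeks recorded at equal rates. No effect could then appear as up to a 25% increase in the equal-rate case. These sizes are illustrative, because fall rates and look-back lengths are assumed. The net direction of the falls comparison is not settled by the text, since it also depends on how the 12-month and 36-week windows are reconciled.

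**What to change.** In section 2.8 and Table 3:

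- Define pre-enrolment falls as those recorded while the participant was resident in the home within the 12 months before enrolment.
- Analyse falls as a rate, with days resident in each period as the exposure (log offset). This also deals with the unequal lengths of the periods.
- State that time not resident is not scored as zero falls.
- Add a falls count for the six-week control period and include it in the pre stage.
- Add a sensitivity analysis restricted to residents with a full 12-month in-home look-back.

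New residents need not be dropped from the main analysis; they contribute whatever resident time they have. The cost is a few sentences of outcome definition, an exposure term, and admission dates, which the home should hold. The downside is that new residents contribute little pre-period information, so the before-and-after comparison will rest mainly on existing residents. The report should say so.
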